## Abstract

**Background:**

The federal and provincial governments in Canada have invested an enormous amount of resources to measure, report and reduce surgical wait times. Yet these measures under-report the wait period that patients’ actually experience, because they do not capture the length of time a patient spends waiting to see the surgeon for a surgical assessment. This unmeasured time is referred to as the “wait one” (W1). Little is known about W1 and the effects that this has on patients’ health. Similarly, it is not understood whether patients waiting for surgical assessment actually want or need surgery. Existing administrative and clinical dataset do not capture information on health and decision-making while the patient is waiting for care form a specialist. The objective of this proposed study is to understand the impact that W1 for elective surgeries has on the health of patients and to determine whether this time can be reduced.

**Methods/Design:**

A prospective survey design will be used to measure the health of patients waiting for surgical assessment. Working with the support of the surgical specialities in Vancouver Coastal Health, we will survey patients immediately after being referred for surgical assessment, and every four months thereafter, until they are seen by the surgeon.

Validated survey instruments will be used, including: generic and condition-specific health status questionnaires, pain and depression assessments. Other factors that will be measured include: patients’ knowledge about their condition, and their desired autonomy in the decision making process. We have piloted data collection in one surgical specialty in order to demonstrate feasibility.

**Discussion:**

The results from this study will be used to quantify changes in patients’ health while they wait for surgical assessment. Based on this, policy- and decision-makers could design care interventions during W1, aimed at mitigating any negative health consequences associated with waiting. The results from this study will also be used to better understand whether there are factors that predict patients’ desire to proceed to surgery. These could be used to guide future research into experimenting with interventions to minimize inappropriate referrals and where they are best targeted.

## Background

Patients typically do not have immediate access to elective surgery in Canada. Instead most patients have to wait, and that wait time is comparatively longer than wait times in other developed countries. Canada ranks as the poorest performer among a sample of 11 industrialized countries in access to hospital care for adult patients; 25% of patients wait more than four months for elective surgery and 41% of patients wait more than two months to see a specialist [1]. For some patients, this wait time impacts their quality of life [2, 3].

Currently, provinces report surgical wait times starting from when patients are placed on the surgical wait list until the time of surgery. This snapshot provides limited insight into the actual duration of a patient’s wait. There is often a lengthy wait from the time a referral to a specialist is made until the time of the initial surgical assessment. This time period, which we refer to as “Wait One” (W1), usually goes unmeasured, but represents an important part of a patient’s care experience.

Little is known about patients’ health while waiting for surgical assessment. Surgeons and referring physicians report that this wait time can be very lengthy and causes a significant disruption in patient’s care [4]. It is not clear how many patients waiting for surgical assessment actually wish to proceed to surgery. A study of patients’ treatment decisions after seeing an orthopaedic surgeon in Ontario reported that 79.3% of patients did not get surgery, indicating that not all referrals may be appropriate for surgical consultation [5]. The study’s authors posited that many referrals to orthopaedics are for specialist input into the management of the underlying condition, and suggest that further research is needed to better understand the kind of patients being referred to surgical specialties and the reasons for those referrals.

### Objective

The objective of this proposed study is to understand the impact that W1 for elective surgeries has on the health of patients and to determine whether this time can be reduced. This objective will be met by answering four research questions:What is the length of time patients spend waiting for their initial surgical assessment?What is the change in health status that patients experience while waiting for their initial surgical assessment?What are patient factors associated with the decision to proceed with surgery?Does self-reported information help to discriminate between warranted and unwarranted referrals?

This study is being undertaken in collaboration with several surgical groups practicing in Vancouver Coastal Health (VCH) authority. This research team has strong historical relationships with many specialty surgical groups practicing in VCH’s six hospitals, the VCH executive team and the British Columbia (BC) Ministry of Health, ensuring the study’s feasibility and maximizing the likelihood that the findings from this study will be incorporated into decision- and policy-making processes.

### A brief review of the literature

#### How long do patients wait for elective surgical assessment?

There are no population-based provincial initiatives that collect patients’ health information while they are waiting for surgical assessment in Canada. Published literature on the period between referral to, and assessment by, a surgical specialty are limited to individual specialties reported at a single instance in time – nor do they study health outcomes or the decision-making processes. In 2005, the Canadian Association of Gastroenterology reported that the median wait time to see one of their specialists for inflammatory bowel disease (which has a two-week target) was 101 days (inter-quartile range 35–209 days) [6]. In 2006, the Canadian Institute for Health Information (CIHI) reported that for patients having hip or knee replacement surgery, 30% of their overall wait was for the initial assessment [7]. Another study of wait times from referral to surgical assessment for hip and knee arthroplasty in Alberta determined that the mean wait time for this period ranged from 51 to 139 days [8]. The study identified that approximately 40-80% of the wait time for patients was during the wait for surgical assessment [8]. One study in Ontario used general practitioner (GP) electronic medical records to track wait times to see a specialist over a five year period [9]. The study found high variability in wait times based on specialty and GP practices, men had a shorter median wait then women (51 and 55 days, respectively) and younger patients had the shortest median wait at 45 days [9].

#### What are the consequences of waiting for elective surgical assessment on patients’ health?

There is an absence of comprehensive data currently available regarding the effects of waiting for elective surgical assessment on patients’ health. This information is crucial, since delays in access to healthcare services for other, non-elective conditions, have been shown to affect the trajectory of care. Research conducted by Prentice and Pizer studying wait times in the Veterans Administration in the United States observed that delays in accessing outpatient services for ambulatory care sensitive conditions, such as surgical assessment, significantly increased the odds of being hospitalized if these delays were over 29 days; if over 31 days, the odds of mortality increased [2, 3].

### Who is waiting for elective surgical assessment?

Critically, there is not much information regarding whether patients waiting for elective surgical assessment really need – or want – surgery. A study in Queensland (Australia) evaluated the effect of implementing a GP referral system aimed at addressing the high wait times for non-urgent specialist appointments [10]. Patients on a wait list who were identified as having long waits were sent letters offering two options: to indicate that the appointment with a specialist for surgical consult was no longer necessary or to update their referral [10]. In the initial stage, 872 patients who had long waits for orthopaedic surgeries were identified and 101 responded, and only 16 of those patients proceeded to surgery [10]. In an expanded program, over 6,885 patients waiting for multiple specialities were contacted. Of these, 633 responded and 197 required surgery [10]. This Australian study helps to underscore that there are a number of patients on the wait list for surgical assessment that may not choose to be, or remain, there.

Taken together, these studies paint a picture of a significant gap in our understanding of the nature of, and changes in, patients’ health and decision making during W1. Addressing this gap in knowledge would provide invaluable insight to patients, clinicians, regional health authorities who manage access to surgical resources and government stakeholders who are ultimately responsible for ensuring effective and efficient use of healthcare spending.

### Conceptual framework

The conceptual basis for this proposal is adapted from a taxonomy proposed by Wennberg et al., in which the utilization of healthcare is classified into one of three categories: effective care, preference-sensitive care and supply-sensitive care [11]. Effective care refers to those clinical scenarios that have an efficacious clinical pathway defined by medical evidence, such as hip fracture repair or appendectomies. This is generally not so for elective surgical care targeted in this study, thus we focus on the latter two categories.

Preference-sensitive care is care for conditions where there is more than one option for treatment and for which the scientific evidence regarding the effectiveness of these options is equivocal [12]. Preference-sensitive care is similar to elective surgical care, where surgery may be one of several treatment options available to the patient. For example, with knee osteoarthritis several non-surgical treatments are available, including weight loss, exercise or steroid treatment. Surgical options for treatment include osteotomy and partial or total knee replacement [13].

In order to provide high quality preference-sensitive care, physicians must take into account a patient’s preference for care and their health goals [12]. This requires that patients be fully informed and have confidence in their decision regarding the treatment choice that best meets their care needs. The quality of referrals for preference-sensitive conditions depends on a patient’s understanding of treatment options, the potential risks for harms and benefits associated with those options and on patient confidence in their decision to have surgery [12]. We define quality referrals as “appropriate”, and no further policy interventions are necessary. Inappropriate referrals do not follow this process.

Supply-sensitive care is care that is based on a local health system’s availability of resources rather than on clinical evidence or a patient’s preference for treatment. Referrals made in this context imply that decisions regarding surgical procedures are based on maximizing available capacity (e.g. operating room time) instead of providing the best care for patients [11, 14]. We consider referrals that do not match patients’ preferences or that are made because of the availability of local surgical resources to be “inappropriate”.

Identifying health system, patient and referring physician characteristics associated with inappropriate referrals for preference- and supply-sensitive surgical care is the basis for this proposed study. Inappropriate referrals to surgical assessment require intervention for two reasons. First, they lead to patients’ unnecessarily occupying space on wait lists for surgical assessment at the expense of patients with appropriate referrals for surgery. Second, inappropriate referrals could be deferred to patient education interventions or active surveillance programs instead of consuming the time and resources of specialists and scarce hospital resources.

The interaction between patients and physicians during the decision to be referred for surgery is governed by their relationship as illustrated on the left half of Figure 1. Referring physicians are often GPs, but may also be other specialists, either within or outside the speciality to which the patient is being referred for surgery. The referring physician is likely familiar with the patient’s medical history, has an established relationship with the patient and may be aware of that patient’s specific health goals or concerns.

**Figure 1 Fig1:**
[figure not shown]
**Conceptual model for the collection and measurement of patients; health data while waiting for surgical assessment.**

Patients’ health goals, well-being, and knowledge level will be factors in their decision to be referred to surgery. Although not all patients wish to be involved in the treatment decision-making process, those that are report greater quality-of-life scores and less regret about their treatment [15, 16]. To understand the role these factors play in referrals and decision to proceed with surgery, this proposed study will measure health, functional well-being and knowledge level at the time of referral for surgery. These measures will be regularly retaken over the course of the W1 period in order to track any changes and their potential impact on a patient’s decision to proceed with surgery.

The interaction between the patient and the surgeon in the decision to proceed with surgical treatment is illustrated on the right half of Figure 1. The patient’s measured level of health, knowledge regarding their condition, and decision confidence may have changed while waiting, thus affecting their decision to proceed with surgical treatment. Using statistical models for repeated measures, we will incorporate changes in patients’ level of health, knowledge regarding their condition and decision confidence over time, and its potential effect on surgical treatment.

Surgeons also play a role in the decision of patients to proceed to surgical treatment. Surgeon effects will be included in our statistical models to reflect treatment preferences, as well as age and utilization profiles. The end point of the study is, based on the surgical assessment, the patient’s decision to proceed with surgical treatment or not. The modalities of treatment prior to referral to surgical assessment are outside of the scope of this study and will be pursued in the future.

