### Data collection procedures

The initial survey will be mailed as soon as verbal consent is received, within a week of the referral being received by the surgeon’s office. Subsequent surveys will be mailed every four months until the participant has their consultation with a surgeon. The last point of survey will be just before the surgical assessment. Patients may have different numbers of survey points because the WI period varies by speciality and surgeon. We will identify which patients progress to surgery with the assistance of the surgeon’s office.

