### Sample size estimation strategy and power analysis

The study will contact each patient referred for a surgical assessment for the surgical specialties included in Table 1. Precise estimates of procedures for power calculations are derive from historical utilization patterns. Based on surgical utilization statistics, there were at least 200 procedures conducted in 2010/2011 for each urology procedure in Table 1, providing 200 potential study patients per year for each procedure, noting that Vancouver General Hospital and St. Paul’s Hospital act as a provincial referral centre for a number of specialized procedures, while other specialties have similar, or greater, number of potential study patients.

This pool of recruits provides a sampling frame of 700 patients for each procedure (of the four year study design, we will recruit patients for 3.5 years). Among these, we expect that we will recruit approximately 48% of patients, leaving the study with 336 patients per procedure. Given our experience in similar studies, we expect to retain 70% of patients throughout the observation period, or observe complete data on 235 patients (equal to 700 times 0.48 times 0.70).

The assumed effect size of 0.2 SD is inferred from previous studies. To detect a treatment effect size over the W1 time of 0.2 standard deviation (SD) on decline in health, and probability of proceeding to surgical treatment, our study will require 220 patients, presuming alpha = 0.05 (two-tailed) and beta = 0.20 (power = 80%). Therefore, relative to our projected recruitment, our study is adequately powered to detect moderate sized effects in each surgery.

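### The end point is the patient's decision after assessment, but the data described record only who goes on to surgery, so refusal cannot be told from the surgeon not offering it

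*Protocol article*

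**What the plan says.** The Conceptual framework section (text after Figure 1) fixes the end point: "The end point of the study is, based on the surgical assessment, the patient’s decision to proceed with surgical treatment or not". The same paragraph accepts that "Surgeons also play a role in the decision of patients to proceed to surgical treatment" and says that surgeon effects will enter the statistical models.

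Two of the four research questions under Objective depend on this outcome: "What are patient factors associated with the decision to proceed with surgery" (question 3) and "Does self-reported information help to discriminate between warranted and unwarranted referrals" (question 4).

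On measurement, Data collection procedures says: "We will identify which patients progress to surgery with the assistance of the surgeon’s office". On survey timing it says: "The last point of survey will be just before the surgical assessment". The article describes no survey after the assessment. It describes no record of whether surgery was offered, whether the patient declined it, or by what date progression is judged.

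On the calendar, the sample size section says: "of the four year study design, we will recruit patients for 3.5 years". Background gives the only figure for the surgical wait: "25% of patients wait more than four months for elective surgery".

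**The concern.** The variable defined and the variable collected are different. A decision is something the patient makes after hearing the surgeon's view. Progression to surgery is the joint result of the surgeon offering and the patient accepting, and possibly also of enough time having passed.

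The study's own framework needs the two kept apart. It calls a referral inappropriate when it does not match the patient's preference or when it is driven by local surgical supply. A patient who declines tells us about preference. A patient who is not offered surgery tells us about surgeon judgement or capacity. If both are coded as not progressing, a characteristic that makes surgeons less likely to offer surgery will look like a characteristic that makes patients less likely to want it. The Discussion proposes building algorithms on such characteristics to direct patients to non-surgical care, so the distinction has practical consequences.

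An analysis plan cannot repair this later. An offer or refusal that nobody recorded cannot be recovered from the survey data.

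**Working it through.** The plan gives no figure on this point to reproduce. The check sets the statements side by side and then sizes the one part that can be sized.

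**1. Can any described data source yield the patient's decision?**
- Surveys: the last is before the assessment, so none can record a decision based on it.
- Decisional Conflict Scale: part of those surveys. It measures certainty before the visit, not the choice made there.
- Surgeon's office: reports progression only, as far as the article says.

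None does.

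**2. What does a progression variable contain?** For an assessed patient,

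P(progress) = P(offered) × P(accepts | offered).

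Background cites an Ontario orthopaedic study in which 79.3% did not get surgery, so P(progress) = 1 − 0.793 = 0.207. That value fits P(offered) = 0.207 with every offer accepted (no refusals among the 79.3%). It fits equally well P(offered) = 1 with 20.7% accepting (all 79.3% are refusals). Progression data alone cannot place a study between these extremes. Surgeon terms shift the average by surgeon, but within one surgeon's patients the product is still all that is seen.

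For scale, if that rate held among the 235 complete patients projected per procedure, 235 × 0.793 ≈ 186 would be in the undivided category and 235 × 0.207 ≈ 49 would have progressed.

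**3. Timing, only if progression means surgery performed.** Inputs:
- Enrolment uniform over 0-42 months and close at 48 months (sample size section; uniformity assumed).
- Wait for assessment (W1): log-normal with median 55 days (women in the Ontario GP-record study) or 101 days (the gastroenterology report), both from the literature review. Log-SD 0.8 (assumed), or ln(209/35)/(2 × 0.6745) = 1.32 from the gastroenterology inter-quartile range of 35-209 days.
- Wait for surgery (W2): log-normal with 25% over four months (122 days), log-SD 0.6-1.0 (assumed). The median is 122/exp(0.6745 × log-SD), which is 81 to 62 days.
- Every simulated patient chooses surgery, so the results are shares of those who do.

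The quantity of interest is P(enrolment + W1 + W2 > 48 months, given enrolment + W1 ≤ 48 months): assessed and decided, but not yet operated on.

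| W1 median, log-SD | All recruits | Recruited months 36-42 |
|---|---|---|
| 55 days, 0.8 | 2.0-3.2% | 12-15% |
| 55 days, 1.32 | 2.7-3.8% | 14-16% |
| 101 days, 0.8 | 3.6-4.6% | 21-22% |
| 101 days, 1.32 | 3.9-4.9% | 19-20% |

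This gives about 2-5% overall and 12-22% among late recruits. The 55-day rows fit the article better: they imply 45-47% waiting over two months for a specialist, against 41% in Background, whereas the 101-day rows imply 65-74%.

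**4. Patients who leave the list before assessment.** Under the stated end point they have no assessment-based decision. Under the stated ascertainment they would simply not progress. The article does not say which coding applies.

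**The case against.** The strongest reply has four parts.

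*The surgeon's role is acknowledged and modelled.* This is true, and a reader should not infer that it was overlooked. The adjustment works between surgeons, however, and does not reveal why a given patient had no surgery. A joint outcome also partly serves question 4, since a non-offer says something about whether a referral was warranted. It serves question 3 much less well.

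*The article may be a condensed account.* A fuller protocol could record more, and analysis sets and coding rules are commonly placed elsewhere. This stands for the handling of leavers. It does not remove the mismatch between an end point and an ascertainment that are both stated here.

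*Progression need not mean surgery performed.* A reader might infer that only completed operations are captured. The text does not say so; a surgeon's office could equally report booking or consent. The timing component is therefore conditional.

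*The timing loss is easy to overstate.* A reader might count everyone without surgery at month 48, which under the same inputs gives 2.4-13% overall and 15-39% of late recruits. Those totals include patients not yet assessed. They have made no decision and are not people who said yes and were coded as no. In the worst case about 8.5 of the 13 percentage points are unfinished waits for assessment. The upper W1 input also comes from gastroenterology, which is not among the study's specialties.

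A reader might also infer that patients who leave before assessment are dropped from the analysis. Nothing in the article says this.

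**Conclusion.** The concern holds as a mismatch between the defined end point and the described measurement. As written, the study cannot separate patient refusal from surgeon non-offer, so answers to questions 3 and 4 may partly reflect surgeon selection. Neither the size nor the direction of any bias can be given, because the documents do not report the offer/refusal split; that bias is present and large should not be inferred.

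The timing component is secondary: about 2-5% of assessed patients who chose surgery, concentrated in late recruits (12-22%). It rests on the assumed wait distributions and on progression meaning surgery performed. The main point depends on neither. The status of patients who leave before assessment is an open question in the text, not a demonstrated error.

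This should be corrected before data collection, because the missing information may not be recoverable afterwards.

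**What to change.** Reconcile the end point in the Conceptual framework section with Data collection procedures:

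- For each enrolled patient, have the surgeon's office record one dated status: offered and accepted, offered and declined, not offered, or left the list before assessment.
- Define proceeding as offered and accepted at the assessment, and record surgery performed, if wanted, as a separate item.
- State how patients who leave before assessment are coded.
- Report refusal and non-offer separately where numbers allow.

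The cost is one extra coded item for the surgeons' offices and a short change of wording. The offices already share referral data and help identify progression, so the burden should be small. That they can supply this item routinely is an assumption to confirm with them. Separate reporting will be imprecise for any procedure in which one of the categories is small.
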